### Variables, outcomes, and study measures

Epidemiologic information will be collected for each study participant for their entire clinical course at all associated study sites, including: patient demographic information (e.g., age, sex, race, and comorbidities); injury details (e.g., time, type, and intent); facility data (e.g., hospital name, trauma level, clinician qualifications, units of care); clinical data (e.g., vital signs, medications administered, critical interventions, operations performed); and, trauma system process (e.g., key dates and times [51]). Table 2 describes the exposures, predictors, and outcomes of interest in the EpiC study.

**Table 2 Tab2:** Key EpiC Study Exposure, Predictors, and Outcome Measures

Exposures	Definition	Variable Type	Data Source
1^O—^Critical resuscitative interventions (CRI)	Prehospital and in-hospital resuscitative interventions or therapeutics, delivered for the patient’s traumatic injury (e.g., thoracostomy for tension pneumothorax), within the first 24 h post-injury	Binary	EMS and/or Hospital
1^O^—Trauma-to-CRI time	Duration of time from injury to receiving a critical resuscitative intervention for the dominant injury	Continuous	EMS, Hospital, and/or Pathology

Predictors	Definition	Variable Type	Data Source
Age	Span of years lived at the time of injury	Continuous	EMS, Hospital, or Pathology
Sex	Biological sex given at birth	Categorical	EMS, Hospital, or Pathology
Comorbidities	One or more pre-existing disease or conditions present in the patient that are trauma-relevant chronic conditions (e.g., bleeding disorder)	Binary	EMS or Hospital
Socioeconomic status	Based on hospital insurance status	Categorical	Hospital
Mechanism of injury	Main force that created the injury or how injury was inflicted (e.g., firearm, Struck/hit, stabbing or cut, vehicular injury, fall, thermal, choking/hanging, iatrogenic, other)	Categorical	EMS, Hospital, or Pathology
Provider level	Health care provider qualifications (e.g., rank of EMS provider, type of doctor)	Categorical	EMS
Injury severity	ISS calculated as the sum of squares of 3 worst AIS scores. Low (< 12) or high (≥ 12)	Continuous, Binary	EMS, Hospital, or Pathology

Outcomes	Definition	Variable Type	Data Source
1^O—^Ambulance death or 7-day in-hospital mortality	All-cause mortality in the ambulance or within the hospital in the first 7-days post-injury	Time-to-event	EMS, Hospital, or Pathology

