2^O^—30-day in-hospital mortality	All-cause mortality at any point during the hospital stay	Time-to-event	Hospital or Pathology
2^O^—Non-resuscitative surgical interventions	Post-injury interventional procedures such as fasciotomies, limb amputation, and laparotomies	Binary	Hospital
2^O^—Secondary infections	Post-injury infections such as wound infections, pneumonia, and sepsis	Binary	Hospital
2^O^—Organ failure	Organ failure will be assessed by individual organ (acute kidney injury, coagulopathy, and acute lung injury) and by a composite multiple organ failure score such the SOFA score up to 7-days	Continuous	Hospital

1^O^ = primary exposure or outcome; 2^O^ = secondary exposure or outcome; Data Source: EMS data is abstracted from WCG EMS Electronic Patient Care Reports, hospital data is abstracted from handwritten medical charts, and pathology data is abstracted from handwritten postmortem/autopsy reports from the Forensic Pathology Service of South Africa. EMS = Emergency Medical Services, ISS = Injury Severity Score, AIS = Abbreviated Injury Scale (anatomical score), SOFA = Sequential Organ Failure Assessment

The primary outcome of mortality will be defined as time to ambulance death or in-hospital death within 7 days of injury. The definition of examining mortality within 7 days was previously selected by a 20-person expert trauma panel to be the ideal duration to assess deaths for a study focused on the effects of early trauma resuscitation [52]. A study of three trauma-focused randomized controlled trials in urban U.S. settings have demonstrated that most hemorrhagic deaths occur in hospitals and within 6 h of patient encounter [51]. However, in our setting we examine a longer window since early deaths are more likely to occur at the scene due to the higher prevalence of penetrating injuries and fewer ambulance resources, and consequently later deaths will likely occur post-EMS transfer and hospital arrival. We will define the secondary outcomes of 24-h and 30-day mortality as time to in-ambulance or in-hospital mortality from injury. Other secondary outcomes include patients’ morbidity and need for operative interventions (those that are not considered damage control surgery), secondary infections (including wound infections, pneumonia, and sepsis), and organ failure (defined with the Sequential Organ Failure Assessment (SOFA) Score [53, 54]).

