The primary exposures of interest are the delivery of CRI and trauma-to-CRI time. The delivery of CRIs will be defined as the performance of a resuscitative intervention (airway, breathing, circulatory, or neurologic) within the first 24-h from the time of injury. The trauma-to-CRI time will be defined as the duration from experiencing the injury to receiving a critical resuscitative intervention, which could occur at the trauma centre, a transferring hospital, or in the ambulance (in limited cases). To assess our secondary objective, we will additionally consider the individual resuscitative interventions as separate exposures of interest.

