### Assessing association with morbidity outcomes

Analyses for morbidity outcomes will be conducted using multivariable generalized linear models (GLMs) with the appropriate link function chosen based on the outcome [67]. To account for potential informative censoring by the competing risk of death, we will use a weighted GLM with inverse probability of censoring weights (IPCW) [68, 69] and will compute robust standard errors. IPCW will be estimated from a logistic regression with the outcome of availability of morbidity information and predictors related to the morbidity and mortality (e.g., patient risk factors). In the weighted GLM, the association between delivery of CRI and morbidity outcomes will be assessed by including and testing the effect of a binary indicator for treatment. The effect of trauma-to-CRI time will be investigated using flexible, potentially non-linear (e.g., sigmoidal, exponential, piecewise) relationships.

For the secondary objective, we will examine the effect of individual resuscitative interventions on morbidity outcomes in treated patients using similar GLMs with intervention and time-to-CRI defined based on the specific treatment. Analysis will be performed in appropriate subgroups (e.g., injury type, injury severity) for injury-specific interventions.

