### Power calculation

Based on a conservative estimate from the smallest hospital, we assume an average of 3,600 cases from each of the four hospitals in a 4-year period. Thus, we anticipate a total sample size of 14,400 cases over the study period. We assume that 30% of cases have an average trauma-to-CRI time within 2 h of injury and an average 7-day mortality of 10% for the primary mortality outcome. From a Cox proportional hazards regression, with 80% power (alpha = 0.05, two-sided) we can detect a hazard ratio of 0.85 for trauma-to-CRI time within the first 2 h versus not. For the morbidity outcomes, we present the power calculation for a continuous outcome (organ failure), and a binary outcome (wound infection). For the continuous outcome of organ failure, assuming the standard deviation of the SOFA score is 4 [71], with 80% power (alpha = 0.05) we can detect a mean decrease in score of 0.20 in those with trauma-to-CRI time within the first 2 h versus not, which corresponds to a standardized effect size of 0.05. For the binary outcome indicating whether a wound infection occurred, if 10% of cases with a trauma-to-CRI time within 2 h have a wound infection, with 80% power (alpha = 0.05, two-sided) we can detect an odds ratio of 0.84 for trauma-to-CRI time within 2 h versus not.

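### Organ failure is defined and powered on SOFA, and some of the resuscitative interventions under study may themselves add SOFA points

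*Protocol article*

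**What the plan says.** **Outcome.** Table 2 of the protocol article (Variables, outcomes, and study measures) has two parts for organ failure: "Organ failure will be assessed by individual organ (acute kidney injury, coagulopathy, and acute lung injury") and a composite, "by a composite multiple organ failure score such the SOFA score up to 7-days". The text below the table is narrower and gives "organ failure (defined with the Sequential Organ Failure Assessment (SOFA) Score") as the definition. A 7-day end is stated for the score, but no start.

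**Exposure.** Delivery of a CRI is "the performance of a resuscitative intervention (airway, breathing, circulatory, or neurologic) within the first 24-h from the time of injury". Table 2 describes CRIs as "Prehospital and in-hospital resuscitative interventions or therapeutics, delivered for the patient’s traumatic injury (e.g., thoracostomy for tension pneumothorax"). Thoracostomy is the only CRI named as an example.

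**Analysis.** Under Assessing association with morbidity outcomes, "the association between delivery of CRI and morbidity outcomes will be assessed by including and testing the effect of a binary indicator for treatment". For the secondary objective, "we will examine the effect of individual resuscitative interventions on morbidity outcomes in treated patients using similar GLMs".

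**Power.** For SOFA with an SD of 4, the Power calculation section states that "we can detect a mean decrease in score of 0.20 in those with trauma-to-CRI time within the first 2 h versus not", a standardized effect of 0.05.

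**The concern.** Exposure and outcome may share content. The article does not reproduce the SOFA items, so the following is an assumption about the instrument it names: the upper respiratory grades require ventilatory support, the upper cardiovascular grades are set by vasopressor use, and the neurologic item is the Glasgow Coma Scale (GCS), which sedation and intubation lower. If the CRI list includes support of this kind, a treated patient can score higher than an equally injured untreated one because of the treatment, not because of worse organ function.

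The planned adjustments address other problems. Covariate adjustment deals with confounding, and the inverse probability weights deal with morbidity data lost to death. Neither removes points that the treatment itself contributes.

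The Objectives section hypothesizes that failure to deliver CRIs worsens morbidity. In a comparison with untreated patients, the overlap works against that hypothesis: it could hide a real benefit or produce a false signal of harm. The analyses of single interventions are also exposed, because an airway or breathing intervention may be regressed on a score that contains ventilatory support.

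**Working it through.** **Inputs from the Power calculation section.** N = 14,400; 30% with CRI within 2 h; SD 4; 80% power; alpha 0.05. Sidedness is not stated for SOFA; two-sided is assumed, as for the other two outcomes.

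**Step 1: reproduce the plan's figure.**
- Groups: 0.30 × 14,400 = 4,320 and 0.70 × 14,400 = 10,080.
- Standard error: 4 × √(1/4,320 + 1/10,080) = 0.0727.
- Detectable difference: (1.960 + 0.842) × 0.0727 = 0.204 points, or 0.204/4 = 0.051 SD. These round to the stated 0.20 and 0.05.
- Power at exactly 0.20: Φ(0.20/0.0727 − 1.960) = 78.5%.

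The arithmetic is sound. The figure reproduces with all 14,400 cases in the two groups, so the comparison group may include patients who never received a CRI.

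**Step 2: size of a scoring overlap.** Let f be the excess share of exposed patients, over the comparison group, who gain points from the treatment itself, and k the points gained. The exposed mean rises by f × k. Neither f nor k is in the documents; both are assumptions and are varied below.

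Share that offsets the full 0.20, f = 0.20/k:

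| k (points) | f |
|---|---|
| 1 | 20% |
| 2 | 10% |
| 3 | 6.7% |
| 4 | 5% |

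**Step 3: effect on inference.** With a true benefit of 0.20 and the SD held at 4:
- chance of detecting the benefit = Φ((0.20 − f × k)/0.0727 − 1.960);
- chance of significant apparent harm when there is no true effect = Φ(f × k/0.0727 − 1.960), nominally 2.5%.

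| f | k | Shift (points) | Benefit detected | False harm, no true effect |
|---|---|---|---|---|
| 0 | – | 0 | 78.5% | 2.5% |
| 1% | 1 | 0.01 | 74.3% | 3.4% |
| 2.5% | 2 | 0.05 | 54.1% | 10.2% |
| 5% | 2 | 0.10 | 27.9% | 27.9% |
| 10% | 2 | 0.20 | 2.5% | 78.5% |
| 5% | 4 | 0.20 | 2.5% | 78.5% |

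**Step 4: which contrast.** The 0.20 target belongs to the timing contrast. The article gives no detectable SOFA difference for CRI versus no CRI, so for that comparison 0.20 is only a yardstick. If the later group includes untreated patients, the shift in the timing contrast runs toward harm. If both groups were treated, f is a net difference between two treated groups and may have either sign.

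**The case against.** The strongest objection is that the mechanism is not in the article. It lists no SOFA items and mentions no intubation, sedation or vasopressor. Scoring conventions could sit in the data dictionary, which is not shown. This stands as a limit: the point is conditional on standard SOFA scoring and on what the CRI list contains. It does not remove the point, because the article itself fixes SOFA as the definition and the power basis, and sets an exposure that spans all four resuscitation domains. Both conditions can be checked quickly against the scoring sheet and the CRI list.

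Other parts of the objection also stand:
- A reader might infer that receiving any CRI raises the score. The article does not support that. Only CRIs that are also scoring criteria could do so, and thoracostomy is not shown to be one. The pooled indicator needs only a subset of such CRIs to be affected, but the size of that subset is unknown.
- A reader might infer that total SOFA is the only organ-failure measure. Table 2 also plans individual-organ outcomes and introduces SOFA as an example of a composite.
- A reader might infer bias toward harm in every contrast. Among treated patients the direction is uncertain.
- The combination of 5% and 4 points is an extreme case, with every affected patient moving from 0 to the maximum of one item. At 1 point each, 20% would be needed.
- Dropping total SOFA would remove domains that CRIs are meant to improve. That is a trade-off, so demoting the score outright is not warranted.

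**Conclusion.** The point holds in conditional form. Organ failure is defined and powered on SOFA, the exposure covers the kinds of support that standard SOFA scoring counts, and nothing shown starts scoring after the 24 h in which the exposure is delivered. If some CRIs are scoring criteria, comparisons with untreated patients shift toward apparent harm.

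The actual size cannot be computed from the documents. What can be shown is sensitivity: the target is 0.05 SD, so an assumed shift of 0.05 points lowers the chance of detecting a true 0.20 benefit from 78.5% to 54%, and a shift of 0.20 removes it. A shift of 0.01 costs only about 4 percentage points (78.5% to 74.3%).

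The stated power figure is not in error, and the primary 7-day mortality analysis is untouched. This concerns one secondary outcome, but the remedy is cheap and worth making.

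**What to change.** 1. Keep total SOFA. Prespecify beside it a SOFA analysis that omits or re-scores the treatment-defined criteria: the ventilatory-support grades, the vasopressor grades and GCS recorded under sedation.
2. Base the interpretation of the CRI effect on organ failure on that analysis together with the acute kidney injury and coagulopathy outcomes already in Table 2.
3. List which CRIs are also SOFA scoring criteria.
4. Start SOFA scoring after the 24-h exposure window. This alone is not enough, because support begun as a CRI may continue beyond 24 h; item 1 is still needed.
5. State whether the group without CRI in the first 2 h includes patients who never received one.

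**Cost.** A change to the outcome wording and a little more analysis. The modified score is less comparable with studies reporting total SOFA, and the SD of 4 must be restated for it. Re-scoring depends on charted GCS, medications and interventions; the Limitations section already warns of missing and hard-to-read handwritten records, so some patients may not be re-scorable.

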### Assessing association with mortality outcomes

Time-to-event analyses will be used to estimate the association between delivery and trauma-to-CRI time with mortality outcomes. This approach allows us to (1) systematically follow a representative cohort of injured individuals that are alive at the initial request for medical attention with moderate to high baseline risks, and (2) produce valid estimates of the timeliness and effectiveness of the urgent care initiated within the regional trauma system for these individuals [57]. Multivariable Cox proportional hazards models with a time-dependent covariate for CRI will be used to study the effect of receiving CRI during different time periods post-injury (e.g., 0–2, 2–12, > 12 h). We will assess model fit and the proportional hazards assumption. We will consider alternative model specifications as necessary, including a left truncated Cox proportional hazards model [58, 59], joint modelling of CRI and death [60–62], and estimating the survivor average causal effect (SACE) [63–66].

The secondary objective of assessing the effect of the delivery and timing of individual resuscitative interventions that occur during clinical course will be evaluated using similar models. Some interventions are injury-specific, and thus analysis will be performed in appropriate subgroups (e.g., by injury type and injury severity).

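### The morbidity model tests CRI delivery over 24 h as a fixed yes/no indicator, with no stated rule that organ failure must follow the CRI, so the delivery contrast is biased against CRI.

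*Protocol article*

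**What the plan says.** All references are to the protocol article.

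- **Exposure** (Variables, outcomes, and study measures): CRI delivery is binary and means a resuscitative intervention performed "within the first 24-h from the time of injury".
- **Outcome** (same section, Table 2): kidney injury, coagulopathy and lung injury are each taken separately, alongside "a composite multiple organ failure score such the SOFA score up to 7-days". The row gives an end to the window. It gives no start, no baseline score and no requirement that onset follow the CRI.
- **Morbidity model** (Assessing association with morbidity outcomes): delivery enters the weighted regression as follows: "the association between delivery of CRI and morbidity outcomes will be assessed by including and testing the effect of a binary indicator for treatment". Trauma-to-CRI time is modelled separately with flexible curves.
- **Weights** (same section): "To account for potential informative censoring by the competing risk of death, we will use a weighted GLM".
- **Mortality model** (Assessing association with mortality outcomes): "Multivariable Cox proportional hazards models with a time-dependent covariate for CRI will be used".
- **Adjustment** (Statistical methods and Table 2): the characteristics named include anatomical injury severity but no organ function or physiology before the CRI. The list in Statistical methods is given as examples.

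**The concern.** On day 1 the exposure is still accruing and, on the natural reading, the outcome already counts. Nothing puts the two in order. A patient with coagulopathy at hour 3 who receives a circulatory intervention at hour 6 is analysed as a treated patient with organ failure, although the organ failure came first and may be why the CRI was given. The weights cannot repair this, because they concern whether morbidity is observed, not which event came first.

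The error runs against CRI. The study's hypothesis is that failure to deliver CRIs worsens morbidity, so the bias can shrink, hide or reverse the association the study looks for. The mortality model avoids the same problem through its time-dependent covariate. The delivery contrast for morbidity has no counterpart.

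**Working it through.** **1. The plan's own figure.** Power calculation section: N = 14,400, 30% with CRI within 2 h (4,320 versus 10,080), SOFA standard deviation 4, 80% power, two-sided alpha 0.05.

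(1.960 + 0.842) × 4 × √(1/4,320 + 1/10,080) = 0.204, against the stated 0.20. The figure reproduces. The point concerns time order, not arithmetic.

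**2. Inputs for the size of the bias.** From the protocol: 30% treated by 2 h and the 24-h exposure window. Assumed, because the protocol gives no figures: 50% treated by 24 h; a share p = 2-6% with organ failure onset in the first 24 h, spread evenly; a CRI rate multiplied by m = 1.5-3 after onset; later onset in 6% of the remainder; no true CRI effect; no covariate adjustment.

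**3. CRI rate without organ failure.** To 2 h: −ln(0.70)/2 = 0.1783 per hour. From 2 to 24 h: ln(0.70/0.50)/22 = 0.01529 per hour. The cumulative rate H(t) reaches ln 2 at 24 h.

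**4. Chance of staying untreated after onset at time t.** It is 0.5^m × exp[(m − 1)H(t)], averaged over t to give q. For m = 2:

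- mean of exp[H(t)] = [(1/0.70 − 1)/0.1783 + (1/0.70)(0.70/0.50 − 1)/0.01529]/24 = (2.403 + 37.363)/24 = 1.657
- q = 0.25 × 1.657 = 0.414, against 0.50 without onset.

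**5. Odds ratio for delivery within 24 h.** With L = 0.06(1 − p), and patients without organ failure split evenly between treated and untreated:

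OR = [p(1 − q) + 0.5L]/[pq + 0.5L]

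For p = 0.04 and m = 2: (0.04 × 0.586 + 0.0288)/(0.04 × 0.414 + 0.0288) = 0.0522/0.0454 = 1.15.

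**6. Odds ratio for CRI within 2 h versus not.** Only onset before 2 h (2/24 of early onsets) can prompt a CRI before 2 h. For m = 2:

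- probability of CRI by 2 h after such an onset = 1 − 0.49 × 2.403/2 = 0.411
- over all early onsets: (2/24) × 0.411 + (22/24) × 0.30 = 0.309
- odds with organ failure: (0.04 × 0.309 + 0.0576 × 0.30)/(0.04 × 0.691 + 0.0576 × 0.70) = 0.436
- divided by 0.30/0.70 = 0.429, this gives 1.02.

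| Early onset p | Rate multiplier m | q | OR, delivery in 24 h | OR, within 2 h vs not |
|---|---|---|---|---|
| 2% | 1.5 | 0.454 | 1.05 | 1.01 |
| 4% | 2 | 0.414 | 1.15 | 1.02 |
| 6% | 3 | 0.349 | 1.37 | 1.04 |

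A simulation of the same set-up gave 1.05-1.38 and 1.01-1.04, which agrees within simulation error.

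**7. If CRI truly halves organ failure onset in the first 24 h** (simulated, same settings): the fixed indicator gives 0.95 to 1.12, the within-2-h contrast 0.81 to 0.90, and a 24-h landmark about 1.00.

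**8. Scale for SOFA.** The bias is roughly the excess share of treated patients with organ dysfunction before the CRI, times the points they carry into the score. Assumed combinations of 5% × 4 points, 10% × 2 points or 20% × 1 point each give 0.20. The stated 0.20 belongs to the 2-h contrast. For delivery with an assumed 50/50 split, the detectable difference would be 2.802 × 4 × √(2/7,200) = 0.19, so the comparison of scale carries over.

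**The case against.** **The start of the outcome window is not stated.** A reader might infer that the protocol fixes organ failure as counted from injury. It does not. Injury is the natural time zero because the primary outcome is "time to ambulance death or in-hospital death within 7 days of injury" and the CRI window also runs from injury, but an unseen data dictionary or analysis plan could set SOFA days and baseline values. This stands as a condition on the point. It does not remove it: the article itself fixes the 24-h exposure, the day-7 end and the fixed indicator, and any window opening before hour 24 without an ordering rule has the defect.

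**The bias could be made to look larger.** A constant CRI rate reaching 50% at 24 h gives odds ratios of about 1.08 to 1.6. That rate treats only 1 − 0.5^(2/24) = 5.6% by 2 h, against the protocol's 30%, so the larger figures are not used here.

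**The powered contrast is a different one.** A reader might infer that the bias also undermines the comparison of CRI within 2 h versus not. In the hour-3, hour-6 example that patient is in the later group with or without the CRI, and step 6 shows little distortion. The objection stands: the point is confined to delivery.

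**The odds ratios are crude.** The planned models are multivariable, the adjuster list is open, and vital signs are collected, so adjustment could absorb part of the bias. This is fair. No adjuster named in the protocol, however, measures organ function before the CRI.

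**Survival and infections.** Patients must survive long enough to be treated, but the calculation contains no deaths, so no size is claimed for that. A reader might extend the point to secondary infections. The documents give no ground for supposing that infection precedes and prompts a CRI, so that extension is not supported.

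**Conclusion.** The concern holds for CRI delivery analysed against organ failure, provided the outcome window opens before hour 24. The stated method lets organ failure that prompted a CRI count as its consequence, and the direction is against CRI whenever early organ failure raises the chance of receiving one.

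Under the stated assumptions, of which only the 30% by 2 h comes from the protocol, a CRI with no effect shows a crude odds ratio of about 1.05 to 1.37. A true halving of early organ failure could appear as anything from 0.95 to 1.12. The actual size cannot be known from the documents. The within-2-h contrast, on which the power statement rests, is close to unbiased on this account (1.01 to 1.04), and no sample-size figure changes.

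**What to change.** - **Individual organ failures:** classify CRI exposure by time, counting a patient as treated only from the CRI onward, as the mortality model does. Onset before the CRI then belongs to untreated time.
- **SOFA:** use a score taken after the exposure, adjusted for the earliest recorded score (before the CRI where available).
- **Outcome window:** state when it starts.
- **Sensitivity analysis:** report a 24-h landmark analysis in patients alive and free of that organ failure at 24 h. A reader might prefer it as the main analysis because it removes the overlap. It should not be, because it cannot show any CRI effect on organ failure in the first 24 h: a true halving in that period returns about 1.00.

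The cost is a little more analysis work and reliance on recorded onset times, which come from handwritten hospital charts. Sample size and eligibility do not change. The time-ordered analysis removes the ordering error, not all confounding by indication.
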